### Power analysis and sample size

The sample size is calculated based on a between-arm comparison of the primary outcome – change in SGRQ total score over four months – and to allow for a comparison between rural vs. urban Veterans within the intervention group. In order to have adequate power for the comparison between rural vs. urban Veterans within intervention group, randomization is done in a 2:1 proportion to the intervention arm. We made the following assumptions, all of which are supported by the literature. First, as the minimal clinically significant mean change is SGRQ of 4 units [55], we assume at least a 4-point drop in SGRQ in the intervention arm, a conservative estimate of what might be expected with pulmonary rehabilitation or physical activity interventions in patients with COPD [56,57]. In contrast, wait list controls are expected to experience some deterioration in SGRQ even over a short period of time. In one study of 624 patients with COPD, SGRQ steadily worsened over time with an increase of approximately 2 units per year. The reported standard deviation of the change in SGRQ is approximately 10 for the intervention and wait list control groups over four-months. Thus to detect with 80% power a conservatively estimated between-arm difference in mean change of 4.3 units using a two-tailed 0.05-level test based on regression analysis and assuming a 2:1 ratio of enrollment, we estimated that 192 evaluable participants would be needed in total, with 128 randomized to the intervention arm and 64 to the control arm. The proposed sample size would provide 80% power to detect a difference within intervention arm between rural vs. urban Veterans of 5 units or larger assuming a standard deviation of 10. Assuming a 20% dropout rate, a total of about 240 participants will be recruited.

### Monitoring and reporting of adverse events

Participants can report an adverse event (AE) by phone, website, or email, and are invited to do so every 30 days. The AEs are tracked electronically in a participant management system and classified as serious if they require hospitalization or result in significant disability or classified as minor if they result in minimal or no disability and do not require hospitalization.

### Ethical and additional safety provisions

Ethical approval for this study was granted by the VA Ann Arbor Healthcare System Human Studies Sub-committee. Additionally, unsupervised home-based exercise programs in the chronically ill elderly require the design of safety provisions to maximize the positive impact, while decreasing the chances of adverse events. The current clinical trial includes preventative measures to increase safety, such as pre-inclusion evaluation and clearance by the personal physician, educational content on the website about the proper shoes and socks to wear, and weather-related recommendations. In order to prevent inappropriate or offensive interactions online, all community posts are reviewed for content within 48 hours and removed if the research staff considers the post offensive or hostile or to protect personally identifying health information. Participants can also report concerns about other participant’s posts to the study staff.

### Analysis plan

Descriptive statistics including proportions or means and their standard deviations are used, when appropriate, to describe various participant characteristics by study groups, such as demographics, symptoms, place of residency (rural vs. urban), and SGRQ scores at baseline (randomization) as well as outcome variables including changes in SGRQ total scores at 4 months and one year. The primary aim is to compare HRQL at four months and at one year in the intervention group compared to the wait list control group whose exposure to the intervention is delayed. Analyses will use the intent-to-treat approach in which the person is considered to be in his/her randomly assigned condition no matter how much he/she participates in it. Separate regression analysis will be done using changes in SGRQ from baseline to four months as the response variable and also using changes from baseline to one year as the response variable. Each regression model will include as primary predictor an indicator for the intervention group and will be adjusted for the baseline values of the response variable and the balancing factors of breathlessness and place of residence. The SGRQ is normally distributed in the COPD population and has true interval scale properties, and thus it is appropriate as a response variable in regression analyses [58]. Additionally, baseline characteristics including age, sex, COPD severity, baseline step counts, and current smoking status will be tested for any imbalances between study groups and/or for potential confounding and will be included in the regression model as appropriate to adjust for confounding.

For the secondary outcome of number of days of hospitalization during the year following randomization, we will use a Poisson regression or a negative binomial regression to make the between-group comparison, with days of hospitalization as the outcome variable, number of follow-up days as the offset variable, and an indicator for the intervention arm as the primary predictor. The model will be adjusted for breathlessness, place of residence and potential confounders, including age, sex, and COPD severity. Additional secondary analyses will examine ER visits, days of hospitalization for COPD-specific diagnoses, ICU days, and total number of admissions using the same methods.

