## Background

### Burden and management of COPD

Chronic Obstructive Pulmonary Disease (COPD) is a significant problem worldwide, affecting 9-10% of the population 40 years of age or older [1,2]. In the U.S., COPD is currently the third cause of mortality [3] and affects 5.1% of the population. Among Veterans the prevalence is 8.2% [4] with those afflicted by the disease accumulating more emergency room and outpatient visits to physicians when compared to persons without COPD. COPD is characterized by acute exacerbations (AECOPD), which are responsible for 70% of the total cost generated by the disease. AECOPD accelerate the rate of decline of lung function [5] and negatively impact health-related quality of life (HRQL); nearly 50% of the patients will continue to need help with their activities of daily living six months after hospital discharge for an AECOPD [6]. AECOPD are part of a downward spiral in functionality and HRQL and are also the main risk factor for new or recurrent exacerbations [7].

The principles of COPD management include control of symptoms, prevention of AECOPD, and improving HRQL. Strategies include smoking cessation, pharmacological therapy with short- and long-acting bronchodilators and anti-inflammatory inhaled medications, oxygen supplementation, and early recognition of symptoms. Almost all available therapeutic options have been proven to reduce symptoms, decrease the frequency of exacerbations, and improve HRQL [8-11], but none of the available pharmacologic interventions modifies the progressive loss of pulmonary function [12]. The recognition of a high frequency of cardiovascular disease as cause of death in COPD patients [13] and the role of comorbid conditions as risk factors for recurrent exacerbations has strengthened the interest in the management of other coexistent conditions as an alternative to improve the prognosis of patients with COPD [14], or to develop COPD self-management programs [15]. Engagement in physical activity is a cornerstone of self-management programs to improve health status.

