### Baseline measures and randomization

After completing the online screening and informed consent, participants complete online surveys about the primary outcome of HRQL using the St. George’s Respiratory Questionnaire and the general health status question from the SF-36. The surveys also assess demographics; health history including comorbidities and COPD hospitalizations; motivations and barriers for walking; knowledge and attitudes about COPD, current cigarette smoking, current supplemental oxygen use, the Modified Medical Research Council (MMRC) dyspnea score, depression, social support; and comfort with computers. Once the baseline survey is complete, study staff mail participants an Omron pedometer (HJ-720 ITC) with a USB upload cable and instructions about uploading pedometer data and pedometer care and use. This pedometer has been previously validated in a similar population [44]. Participants are asked to wear their pedometers throughout the day for seven days to assess their baseline step counts. Pedometers have a sticker over the display during the baseline assessment period, and no step-count goals or feedback are provided during this stage. At the end of the seven days the participant uploads their pedometer data using the USB cable and their computer. Immediately after completion of baseline pedometer data collection and receipt of the medical clearance, the participants are automatically randomized to one of two arms: 1) Internet-mediated, pedometer-enhanced program (Taking Healthy Steps) or 2) Wait list control. Randomization is stratified by breathlessness (defined by MMRC) and urban vs. rural residence.

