### Outcomes and data collection procedures

The *primary outcome* is change in Saint George’s Respiratory Questionnaire (SGRQ) Total Score at 4 and 12 months compared to baseline. The SGRQ is a well validated disease-specific HRQL measure [48] widely used in clinical trials of pulmonary rehabilitation, disease management interventions, and exercise [49] in patients with COPD. SGRQ will be measured at baseline, four months, and one year after randomization.

Hospitalizations for AECOPD, self-reported dyspnea, and change in average daily step counts will be *secondary outcomes*. To ascertain hospital admissions, a two-way process will be performed, using both self-reported hospitalizations (which capture non-VA admissions) and identifying hospital admissions through the VA administrative databases. ICD-9 codes will be used to identify cause of admission. AECOPD will be defined by a previously validated combination of inpatient and outpatient ICD-9 codes [50], and validated algorithms will also be used to identify pneumonias and episodes of respiratory failure [51,52]. Dyspnea is measured with the MMRC Dyspnea Score [53,54]. Change in average daily step counts will be calculated using 7 days where at least 5 of the 7 days have at least 100 steps and 8 hours of activity. Goal commitment (percentage of intervention days during which step-count goals are achieved, as well as self-reported goal commitment and perceived difficulty of goal level evaluated by the Likert scale and open-ended questions) and participant retention are also secondary outcomes. Endpoints are evaluated at baseline, four months, and one year after randomization.

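### The plan permits ordinary Poisson regression for days in hospital with no choice rule or variance correction; if used with model-based standard errors, the intervals would be much too narrow

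*Protocol article*

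**What the plan says.** The Study aims section of the protocol article makes estimation of the effect on all-cause hospital days over one year the second aim. The Analysis plan treats it as a secondary outcome and states: "we will use a Poisson regression or a negative binomial regression to make the between-group comparison". The response is each participant's count of hospital days, and time under follow-up enters as an offset. No rule selects between the two models, and no overdispersion check, scaled variance or robust variance is mentioned. ER visits, COPD-specific hospital days, ICU days and number of admissions are to be analysed in the same way.

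On covariates the plan says: "The model will be adjusted for breathlessness, place of residence and potential confounders, including age, sex, and COPD severity". Prior hospital use is not named, although the list is open. The section Baseline measures and randomization says that the baseline survey covers "health history including comorbidities and COPD hospitalizations". Admissions during follow-up are found "using both self-reported hospitalizations (which capture non-VA admissions) and identifying hospital admissions through the VA administrative databases" (Outcomes and data collection procedures).

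**The concern.** Poisson regression with its usual standard errors assumes that the variance of the count equals its mean. Days in hospital break this by construction: one admission contributes several days at once, and many patients are likely to contribute none. The two models that the plan lists can therefore give similar rate ratios with very different intervals, and nothing in the text says which will be reported.

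Aim 2 is an estimation aim, so the interval is the result. Under plain Poisson, a few long stays that fell by chance in one arm could be reported as an intervention effect. COPD-specific days and ICU days cluster within stays in the same way. The mechanism does not apply to ER visits or number of admissions, where one event counts once.

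Three smaller matters sit in the same two sentences of the plan: the scale of the offset, a baseline hospitalization item that is collected but not named as a covariate, and a COPD severity covariate with no stated measure.

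**Working it through.** **The plan's own figures.** The article gives no power, precision, admission rate, length of stay or dispersion for hospital days. Its one sample-size calculation concerns SGRQ and reproduces. With difference 4.3, SD 10, 80% power, two-sided 5% and 2:1 allocation, the control arm needs 1.5 × (1.96 + 0.8416)² × (10/4.3)² = 63.7, so 64. The total is 192, and 192/0.8 = 240. It does not bear on this point.

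**Inputs.** From the article: 155 intervention and 84 control participants randomized; one year of follow-up. Assumed: everything about admissions and stays.

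**Variance of days when admissions are exactly Poisson.** If L is the length of a stay, variance/mean of total days = E[L²]/E[L]. This equals 1 only if every stay lasts one day. For geometric stays with mean m it is 2m − 1:

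- m = 3: 5, and √5 = 2.24
- m = 5: 9, and √9 = 3.00
- m = 7: 13, and √13 = 3.61

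The square root is the factor by which Poisson standard errors are too small. The true size of a nominal 5% test is then 2 × [1 − Φ(1.96/√(variance/mean))], which gives 38%, 51% and 59%. Null simulations with 155 v 84 and an assumed 0.35 admissions per patient-year gave 38%, 52% and 59%. With stays averaging 2 days the simulated figure was 27%.

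**Allowing patients to differ in admission rate.** Let admissions have mean r and variance r + a·r², and let stays have mean m and coefficient of variation c. Then variance/mean of days = m(1 + c²) + a·r·m. Null simulations (155 v 84, 800 replicates each, unadjusted log rate ratio) gave:

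| r | a | m (days) | c | Variance/mean, formula | Variance/mean, simulated median | Empirical SE ÷ Poisson SE | Type I error, Poisson SE | Type I error, empirical-variance SE |
|---|---|---|---|---|---|---|---|---|
| 0.4 | 0.01 | 2 | 0.3 | 2.2 | 2.2 | 1.5 | 21% | 6% |
| 0.2 | 1 | 3 | 0.9 | 6.0 | 5.7 | 2.3 | 41% | 6% |
| 0.4 | 1 | 5 | 0.9 | 11.1 | 10.7 | 3.2 | 56% | 6% |
| 0.8 | 2.5 | 8 | 0.9 | 30.5 | 29.1 | 5.3 | 69% | 5% |

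The first row is deliberately mild. Over the main grid (r 0.2 to 0.8, a 1 to 2.5, m 3 to 8, c 0.9) the SE ratio ran from 2.3 to 5.3. Type I error ran from 41% to 69% with Poisson standard errors and from 5% to 7% with empirical-variance ones. A separate run (0.35 admissions per year, gamma frailty, stays of 3 to 7 days) gave 42 to 59% for plain Poisson, and 5 to 8% for either Poisson or negative binomial with robust standard errors.

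**Offset.** With a log link, exposure enters as log(days). A raw-days offset would make a 30-day difference in follow-up multiply the expected count by exp(30), about 10¹³, against 365/335 = 1.09 on the log scale.

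**The case against.** The article names negative binomial regression, the standard choice for overdispersed counts, so its authors probably foresaw the problem. The choice rule and variance estimator may stand in a fuller plan that is not shown. Every input to the size estimate is assumed, and the outcome is secondary. This is fair as to size and weight. It does not remove the point: the text positively lists plain Poisson as acceptable for an outcome that it does not fit, and no scenario examined makes it acceptable.

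Several stronger readings are tempting but unsupported:

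- **That the offset is wrongly left unlogged.** "number of follow-up days as the offset variable" states no scale. It is ordinary shorthand for exposure, and the raw-days version is too absurd to be what was meant. Only a clarification is needed.
- **That the intervals will be too narrow by a known factor.** This holds only if Poisson is chosen with model-based standard errors, and the factor depends on assumptions.
- **That prior hospitalization is the best predictor and has been ignored.** The background says exacerbations "are also the main risk factor for new or recurrent exacerbations", which concerns exacerbations and not all-cause hospital days. The survey item is COPD-specific, the covariate list is open, and VA databases alone miss non-VA admissions. In a randomized comparison the omission costs precision, not validity. The gain cannot be sized from the article.
- **That COPD severity is not measured.** The Discussion reports no spirometry for confirming the diagnosis. Oxygen use, SGRQ and COPD hospitalizations are collected and could serve as markers. The term is undefined, which is different from unmeasured.
- **That Poisson must be deleted.** Robust standard errors repair it.

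**Conclusion.** The point holds as a conditional one. The Analysis plan leaves open an option that would give wrong error bars for Aim 2 and for COPD-specific and ICU days. If that option were taken with model-based standard errors, intervals would be too narrow by roughly 1.5 to 5 times, and a nominal 5% test would reject about 20 to 70% of the time when there is no effect. The direction follows from days clustering within stays. The size rests on assumed rates of 0.2 to 0.8 admissions per patient-year and mean stays of 2 to 8 days.

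The covariate points are lesser. Naming baseline hospitalization would be consistent with the SGRQ models, which already adjust for the baseline value of the response. The severity covariate needs a definition beyond the MMRC dyspnea score, which already enters as breathlessness. The primary SGRQ analysis and the sample size are untouched.

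**What to change.** 1. Pre-specify one model, negative binomial or Poisson, with robust (sandwich) standard errors, for all-cause, COPD-specific and ICU days.
2. Write the offset as log(follow-up days).
3. Name a baseline hospitalization covariate: either the COPD hospitalization item in the baseline survey, or prior-year admissions from the VA databases plus self-report.
4. State which collected baseline variable stands for COPD severity, for example oxygen use.

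The cost is a few lines in the analysis plan and, if the database route is taken for item 3, one extract from a source already in use. The downside is wider intervals than plain Poisson would show.

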## Results

### Baseline characteristics of participants

Mailed recruitment materials were sent to 28,957 Veterans identified from the administrative database, and 779 provided response and were screened for eligibility (response rate of 2.7%). The most common reason for ineligibility was self-reported moderate physical activity greater than 150 minutes a week. After receiving consent from 307 participants, 239 were randomized: 155 to the intervention and 84 to the wait list control. The recruitment of patients and reasons for exclusion are in the Consort diagram (Figure 2). The demographic, clinical characteristics, baseline step counts, and HRQL measurements are described in Table 1. There was no significant difference in baseline characteristics between the two arms. In general, participants are older (mean age 66.7 ± 8.8); predominantly male (93.7%); self-described as retirees (58.2%) or not currently working (24.7%); and almost half live in rural or remote areas (45.2%); and 25.1% currently smoke. The clinical characteristics include a high number of comorbidities (mean 4.9 per patient), moderate to severe dyspnea in 30.5%, and a total SGRQ score of 46.0 ± 15.4 points. The average baseline daily step counts is 3,497 ± 2,220 steps.

**Table 1 T1:** Baseline characteristics of the participants in taking healthy steps

	**Intervention group (n = 155)**	**Control group (n = 84)**	**Total (n = 239)**	**p-value**
**Demographics**				
Age in years (mean [s.d.])	66.9 (8.7)	66.4 (9.2)	66.7 (8.8)	0.71
Male gender (n [%])	147 (94.8)	77 (91.7)	224 (93.7)	0.33
Race/Ethnicity (n [%])				0.88
*Black*	7 (4.5)	3 (3.6)	10 (4.2)	
*White*	143 (92.3)	79 (94.0)	222 (92.9)	
*Other/combined*	5 (3.3)	2 (2.4)	7 (2.9)	
Hispanic	5 (3.3)	1 (1.2)	6 (2.5)	0.34
**Socioeconomics**				
Community setting (n [%])				0.79
*Urban*	84 (54.2)	47 (56.0)	131 (54.8)	
*Rural*	71 (45.8)	37 (44.1)	108 (45.2)	
Employment (n [%])				0.79
*Retired*	94 (60.7)	45 (53.6)	139 (58.2)	
*Full-Time*	14 (9.0)	7 (8.3)	21 (8.8)	
*Part-Time*	10 (6.5)	6 (7.1)	16 (6.7)	
*Ill, disabled or unemployed*	35 (22.6)	24 (28.5)	59 (28.6)	
*Other*	2 (1.3)	2 (2.4)	4 (1.7)	
Education (n [%])				0.29
*Below high school*	4 (2.6)	2 (2.4)	6 (2.5)	
*High school or GED*	34 (22.2)	11 (13.3)	45 (19.1)	
*Vocational/Technical*	25 (16.3)	11 (13.3)	36 (15.3)	
*Some college*	52 (34.0)	29 (34.9)	81 (34.3)	
*College graduate*	38 (24.8)	30 (36.1)	68 (28.8)	
Annual income (n [%])				0.34
*Below $30 k*	66 (42.6)	35 (41.7)	101 (42.3)	
*$30 to < $40 k*	23 (14.8)	14 (16.7)	37 (15.5)	
*$40 to < $50 k*	21 (13.6)	5 (6.0)	26 (10.9)	
*> $50 k*	24 (15.5)	19 (22.6)	43 (18.0)	
*No answer*	21 (13.6)	11 (13.1)	32 (13.4)	
**Clinical characteristics**				
Ever-smokers (n [%])	146 (94.2)	77 (91.7)	223 (93.3)	0.48
*Current smokers (n [%])*	42 (27.1)	18 (21.4)	60 (25.1)	0.34
Oxygen use (n [%])	35 (22.6)	21 (25.0)	56 (23.4)	0.67
General health (n [%])				0.49
*Excellent, very good*	9 (5.8)	9 (10.7)	18 (7.5)	
*Good*	49 (31.6)	26 (31.0)	75 (31.4)	
*Fair or poor*	96 (61.9)	49 (58.3)	145 (60.7)	
*No answer*	1 (0.7)	0 (0.0)	1 (0.4)	
SGRQ score (mean [s.d.])				
*Total score*	45.5 (15.4)	46.8 (15.6)	46.0 (15.4)	0.54
*Symptoms score*	56.9 (19.4)	56.0 (19.9)	56.6 (19.5)	0.72
*Activity score*	62.1 (20.3)	64.2 (18.0)	62.8 (19.5)	0.44
*Impact score*	32.2 (16.4)	34.1 (17.9)	32.9 (16.9)	0.41
Dyspnea (MMRC score) (mean [s.d.])				0.69
*0-1*	109 (70.3)	57 (67.9)	166 (69.5)	
*2-4*	46 (29.7)	27 (32.1)	73 (30.5)	
Comorbidities (mean [s.d.])	4.8 (2.6)	4.9 (2.6)	4.9 (2.6)	0.82
Baseline step counts				
*Step counts (mean [s.d.])*	3484 (2309)	3521 (2058)	3497 (2220)	0.90

## Discussion

Patients with COPD experience progressive deterioration in their functional status, HRQL, and ability to exercise. Although continuous exposure to tobacco and poor lung function are strong factors related to poor outcomes in this population, the presence of comorbidities has emerged as a significant factor associated with all unfavorable COPD outcomes. Lack of physical activity is both a consequence and a mediator of COPD outcomes, and the success of pulmonary rehabilitation in decreasing hospital admissions, improving HRQL, and decreasing dyspnea has made rehabilitation one of the cornerstones of COPD management. Unfortunately, many barriers limit initial participation in rehabilitation, and there is a need for reinforcement to maintain the gains achieved by patients after completion of a formal program. Veterans with COPD face these barriers, which are complicated by the high frequency of rural residency, comorbidity, and unemployment in this population. Building on previous research that has shown the feasibility of using a pedometer by COPD patients, the accuracy of the device, the ability to individualize and have feedback of an automated intervention, and patients’ favorable views towards participating in online communities, we designed the current pedometer-enhanced, Internet-mediated clinical trial of physical activity for Veterans with COPD. The clinical trial includes unique characteristics such as identification of the pool of potential participants using administrative databases, remote orientation on the use of the pedometer, patient-initiated acquisition of medical clearance for participation, automated web-based data collection, use of multiple communication tools (e.g. pedometer, participation in online communities), and a dynamic, adaptive algorithm for step-count goals.

Our baseline (enrollment) data suggest that by using remote communication tools it is feasible to recruit often hard-to-reach individuals, including: rural and remote residents; elderly subjects; the unemployed; and those with multiple comorbidities [59]. Follow-up at four months and one year are required to evaluate the primary and secondary outcomes (HRQL, step counts, dyspnea, exacerbations and hospitalizations), and the retention and satisfaction with the program. Taking Healthy Steps will also be implemented after one year for wait list controls. Potential limitations of the current design include the low response to the mailed invitation, but this is no different from other studies of investigator-initiated mail contact with COPD patients [27], and the absence of spirometry for confirmation of COPD. In addition, the findings may not be generalizable to women and other patients with COPD who have Internet access but choose not to participate. Participants need some degree of familiarity with the use of computers and information technology, but as the penetration of the Internet within the chronically ill has increased [60], the potential use of the program could increase. Despite these limitations, this study will provide additional answers and insights to further develop, refine, test, and disseminate effective, low-cost behavioral interventions that improve HRQL in the older patients with multiple comorbidities who live in remote areas.

